***PROfit basic***						
Mobilisation and warm-up (5–10 min.)	e.g., range of motion exercises for the wrists, hips, shoulders, knees, and ankles	Cf. session 1–4				
Coordination, balance, and cognitive exercises (10 min.)	e.g., standing balance, bodyweight shifting, motivational cognitive motor games with group interaction including balls and scarfs	Cf. session 1–4	e.g., standing balance with feet together, side-by-side, bodyweight shifting, motivational cognitive-motor games with group interaction including balls and scarfs	Cf. session 9–12	e.g., standing balance with feet together, side-by-side, semi-tandem, tandem, standing on one leg, bodyweight shifting, motivational cognitive-motor games with group interaction including balls and scarfs	Cf. session 17–20
Aerobic walking exercises (20 min.)	e.g., under different single and dual-task conditions, 150 m	Cf. session 1–4, 150–180 m	Cf. session 1–4, 180–210 m	Cf. session 1–4, 210–240 m	Cf. session 1–4, 240–270 m	Cf. session 1–4, 270–300 m
Muscle strengthening exercises (10 min.)	e.g., chair rises, upper body and trunk exercises with additional materials and weights, functional lower-limb exercises	Cf. session 1–4	Cf. session 1–4, extended by individual adjustments of the repetition numbers	Cf. session 9–12	Cf. session 9–12, extended by individual adjustments of the weights	Cf. session 17–20
Cool down (5–10 min.)	e.g., stretching and relaxing exercises	Cf. session 1–4				
***PROfit plus***						
Mobilisation and warm-up (5–10 min.)	e.g., range of motion exercises for the wrists, hips, shoulders, knees, and ankles	Cf. session 1–4				
**Location change 1 (6–8 min.)**	e.g., under different single and dual-task conditions, 50 m	Cf. session 1–4, 50–60 m	Cf. session 1–4, 60–70 m	Cf. session 1–4, 70–80 m	Cf. session 1–4, 80–90 m	Cf. session 1–4, 90–100 m
Coordination, balance, and cognitive exercises (10 min.)	e.g., standing balance, bodyweight shifting, motivational cognitive motor games with group interaction including balls and scarfs	Cf. session 1–4	e.g., standing balance with feet together, side-by-side, bodyweight shifting, motivational cognitive-motor games with group interaction including balls and scarfs	Cf. session 9–12	e.g., standing balance with feet together, side-by-side, semi-tandem, tandem, standing on one leg, bodyweight shifting, motivational cognitive-motor games with group interaction including balls and scarfs	Cf. session 17–20
**Location change 2 (6–8 min.)**	e.g., under different single and dual-task conditions, 50 m	Cf. session 1–4, 50–60 m	Cf. session 1–4, 60–70 m	Cf. session 1–4, 70–80 m	Cf. session 1–4, 80–90 m	Cf. session 1–4, 90–100 m
Muscle strengthening exercises (10 min.)	e.g., chair rises, upper body and trunk exercises with additional materials and weights, functional lower-limb exercises	Cf. session 1–4	Cf. session 1–4, extended by individual adjustments of the repetition numbers	Cf. session 9–12	Cf. session 9–12, extended by individual adjustments of the weights	Cf. session 17–20
**Location change 3 (6–8 min.)**	e.g., under different single and dual-task conditions, 50 m	Cf. session 1–4, 50–60 m	Cf. session 1–4, 60–70 m	Cf. session 1–4, 70–80 m	Cf. session 1–4, 80–90 m	Cf. session 1–4, 90–100 m
***PROfit orientation***						
Mobilisation and warm-up, (5–10 min.)	e.g., range of motion exercises for the wrists, hip, shoulders, knees, and ankles, integrated awareness developing for cardinal points and landmarks with visual aids	Cf. session 1–4	Cf. session 1–4, reduction of the number of optical aids	Cf. session 9–12	Cf. session 9–12, removal of optical aids	Cf. session 17–20
**Location change 1 (6–8 min.)**	Direction pointing task (individually), Landmark recognition task and Landmark sequence task (group-wise), 50 m	Cf. session 1–4, 50–60 m	Cf. session 1–4, 60–70 m	Cf. session 1–4, 70–80 m	Cf. session 1–4, 80–90 m	Cf. session 1–4, 90–100 m
Coordination, balance, and cognitive exercises, (10 min.)	e.g., standing balance, bodyweight shifting, motivational cognitive motor games with group interaction including balls and scarfs, integrated pointing to cardinal directions, assembling sections of facility map, listing the sequence of landmarks within the unit	Cf. session 1–4	Cf. session 1–4, extended number of facility-sections to assemble, landmarks to arrange in sequence from the entire facility	Cf. session 9–12	Cf. session 9–12, extended number of facility-sections to assemble, landmarks to arrange in sequence from outside the facility	Cf. session 17–20
**Location change 2 (6–8 min.)**	Direction pointing task (individually), Landmark recognition task and Landmark sequence task (group-wise), 50 m	Cf. session 1–4, 50–60 m	Cf. session 1–4, 60–70 m	Cf. session 1–4, 70–80 m	Cf. session 1–4, 80–90 m	Cf. session 1–4, 90–100 m
Muscle strengthening exercises (10 min.)	e.g., chair rises, upper body and trunk exercises with additional materials and weights, functional lower-limb exercises	Cf. session 1–4	Cf. session 1–4, extended by individual adjustments of the repetition numbers	Cf. session 9–12	Cf. session 9–12, extended by individual adjustments of the weights	Cf. session 17–20
**Location change 3 (6–8 min.)**	Direction pointing task (individually), Landmark recognition task and Landmark sequence task (group-wise), 50 m	Cf. session 1–4, 50–60 m	Cf. session 1–4, 60–70 m	Cf. session 1–4, 70–80 m	Cf. session 1–4, 80–90 m	Cf. session 1–4, 90–100 m
Cool down (5–10 min.)	e.g., stretching and relaxing exercises	Cf. session 1–4				

*PROfit basic*

*PROfit basic* focusses on daily situations which are commonly associated with increased fall risk. It mainly consists of challenging walking exercises (e.g. brisk walking, starting, stopping, avoiding obstacles, turns). During these exercises, participants are also exposed to a variety of cognitive tasks under dual-task conditions designed to tax specific executive functions and to challenge their focus of attention using acoustic and visual stimuli. Furthermore, exercises for strength, balance, and flexibility as well as endurance performance associated with walking are integrated (cf. Table 2).

There is a focus on everyday skills to promote ADL, cognition and psychosocial resources considering residents’ desires and preferences. For example, by using motivational equipment with different colors during the exercise sessions, a stimulating environment will be provided.
(2)*PROfit plus*

The main structure and contents of the *PROfit basic* intervention will be transferred into the *“PROfit plus” intervention*. In contrast to the basic intervention, the participants will perform the walking exercises throughout the facilities and attend predefined spots in the nursing home. There will be four areas where the activities (1. warm-up/mobilization; 2. coordination and balance; 3. muscle strengthening exercises; 4. cool-down) will be conducted. The walking part of the program will be used to reach these areas. The trainer will check if all participants walk a progressing distance comparable to the *PROfit basic* intervention.
(3)*PROfit orientation*

The *PROfit orientation* intervention integrates navigation and orientation tasks into the walking route including tasks for egocentric and allocentric orientation. The training integrates pointing to specific predefined landmarks (allocentric and egocentric reference frame), remembering the order of landmarks encountered along the route (route knowledge), and navigating to a specific room or area in the facility (planning and navigation). Other navigation and orientation tasks are integrated into the warm-up/mobilization and the coordination, balance, and executive function parts of the training, e.g. pointing or moving to cardinal directions (direction pointing) or assembling sections of the facility map like a puzzle (cognitive map).

Overall, the exercise programs will be continuously adapted to the residents’ capacity and organized as a progressive challenge to expand participants’ resources. This will be done following the FITT principle (Frequency, Intensity, Time, Type) [94] and the recommendations of Herold and colleagues [39] to establish a cognitively beneficial program. These recommendations refer to a regularly performed sequence of structured and progressive physical exercises that are adapted to individuals’ performance limits [39]. Given the different pre-conditions of the participants, adaptions in different domains (e.g. physical or cognitive) are non-linear; trainers have to constantly adjust the program to participants’ abilities. Participants in the wait-list control group will be asked to continue their regular everyday activities for twelve weeks until they receive the intervention type which was randomly assigned to the nursing home (cf. Fig. 2).

**Fig. 2 Fig2:**
[figure not shown]
CONSORT flow diagram for PROfit

### Data collection, management, and analysis

#### Statistical analysis

Descriptive data will be reported as group mean values and standard deviations or medians and interquartile ranges depending on the type of outcome and their distribution. Analysis of baseline differences will be performed using a multivariate analysis of variance (MANOVA). Parametrical and normally distributed measures will be analyzed in separate 4 (group: PROfit basic, PROfit plus, PROfit orientation, wait-list control group) × 3 (test: baseline assessment, post-allocation, close-out-testing) analyses of variance (ANOVA) with repeated measures. If baseline differences are detected, baseline assessment values as well as age and sex discrepancies will be included as covariates in the statistical model. In the case of statistically significant interaction effects, Bonferroni-adjusted post-hoc tests (t-tests, Wilcoxon tests) will be performed to detect statistically significant differences in the groups between baseline- and post-allocation-testing. Kruskal-Wallis and Friedman tests instead of ANOVA will be used for non-parametrical variables and for data for which normal distribution could not be assumed. The effect size will be determined using Cohen’s *f* [95] which is indicative of the effectiveness of treatment and helps to assess whether a statistically significant difference is of practical concern. Cohen’s *f* values are classified as small (0 ≤ *f* ≤ 0.24), medium (0.25 ≤ *f* ≤ 0.39), or large (*f* ≥ 0.40). Additionally, PS_dep_ scores (probability of superiority for dependent samples) will be computed as an estimate of effect size in non-parametrical post-hoc tests [96]. The significance level will be set at *p* < 0.025.

Intention-to-treat analysis will be conducted. For this purpose, data of all participants will be processed in the groups into which they were randomly assigned, regardless of whether they received or adhered to the assigned intervention. The majority of participants are expected to take part in a minimum of 80% of the training sessions. An additional per-protocol analysis will be performed if a sufficient number of participants are lost to outcome assessment or insufficient participation in training sessions. Multiple Imputation will be used to handle missing data assuming that data are missing by chance.

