**Methods:**

A three-arm single-blinded multicenter RCT with a wait-list control group will be conducted in a sample of 513 individuals (needed according to power analysis) in three different regions in Germany. In each nursing home, one of three different intervention approaches will be delivered to participating residents for 12 weeks, twice a week for 45 min each: The *PROfit basic* group will perform functional strength, balance, flexibility, and walking exercises always at the same location, whereas the *PROfit plus* group changes the location three times while performing similar/the same exercises as the PROfit basic group. The *PROfit orientation* group receives navigation tasks in addition to the relocation during the intervention. Physical and cognitive functioning as well as psychological measures will be assessed in all study groups at baseline. Participants will then be randomized into either the intervention group or the wait-list control group. After 12 weeks, and after 24 weeks the measures will be repeated.

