### Trial design

Based on the existing research and the physical training recommendations mentioned above, a multicenter intervention study will be conducted, aiming to determine the feasibility and efficacy of three different exercise intervention programs for residents of nursing homes. The type of intervention program will be randomly assigned to the participating nursing homes. The participants’ allocation to the intervention or wait-list control group will be randomized after baseline assessment in each nursing home. The assessment of primary and secondary outcomes will take place upon entry to the study (T1) by a blinded assessor and will be repeated at twelve (T2) and at 24 weeks (T3) (see Table 1).

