##### Spatial orientation

The Perspective Taking Test is a reliable (Cronbach’s alpha = .82) and valid measure of spatial orientation [70]. It contains a sheet of paper with a consideration of seven objects, which is visible at all times. Each participant gets twelve task sheets with a circle on them. For each task the participants are asked to imagine being at the position of the object in the center of the circle, facing another object, and are asked to specify the direction to a third object [71]. The number of examples, the instructions, and the operation of the test is adapted to the target group of nursing home residents.

To assess landmark recognition, we will adapt the tasks conducted by Deipolyi and colleagues [72], which were already used with cognitively impaired older adults. In this test, participants have to identify which three landmarks out of a set of ten landmark pictures cannot be found in or around the facility. The pictures show landmarks that can be located in the participant’s own room, on the floor level of their own room, inside the facility or outside, close to the facility. Afterwards, the participants have to sort the pictures showing landmarks from their facility by distance, starting from their current position. As the last step, they position the landmarks on an overview map of the facility and surroundings.

Furthermore, a pointing task will be used to ask participants to point to their own room and to six other landmarks in or around the facility, which are also used for the landmark recognition task. Bryant [73] reports that pointing errors significantly correlate with self-ratings of sense of direction (r = − 0.63), worrying about becoming lost (r = 0.51), and mental rotation (r = − 0.39).

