### Interventions

To develop and verify the effect of tailored interventions as well as to meet the criteria of German health insurances [90], several steps are necessary:
Analyzing daily mobility behavior of the nursing home residentsExamining the facilities and relevant landmarksCapturing the wishes and needs for training interventions and activities of the participants as well as barriers for mobility in the specific settingsIdentifying landmarks and structural elements for daily living in the facilitiesIntegrating a)-d) into the interventionsConducting a training curriculum for future trainers in elderly care to gain sustainabilityVerifying the effects on cognitive abilities (especially spatial orientation), physical functioning and psychosocial well-being.

The exercise programs consist of 24 sessions of 45–60 min, conducted twice per week over a period of twelve weeks in groups of up to 15 participants. Exercise sessions will be administered by at least one certified exercise scientist or physiotherapist. The program follows the International Association of Gerontology and Geriatrics (IAGG) guidelines and combines previously published exercises that have proven to be beneficial for cognitive-motor performance in older people in the community and need of care [91, 92].

Based on the previous PROCARE intervention [93], three different programs will be conducted (see Table 2):

**Table 2 Tab2:** Description of the intervention (modified according to Cordes and colleagues [93])

Program	Session 1–4	Session 5–8	Session 9–12	Session 13–16	Session 17–20	Session 21–24

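### The 4 × 3 ANOVA has no term for nursing home although programmes are randomised to homes, so any differing change between homes inflates the group × time and programme-versus-programme tests

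*Protocol article*

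**What the plan says.** The design has two levels of randomisation. Under Trial design, "The type of intervention program will be randomly assigned to the participating nursing homes", while residents' "allocation to the intervention or wait-list control group will be randomized after baseline assessment in each nursing home". The Abstract (Methods) confirms one programme per home: "In each nursing home, one of three different intervention approaches will be delivered to participating residents for 12 weeks". The end of the Interventions section adds that wait-list residents continue their usual activities "until they receive the intervention type which was randomly assigned to the nursing home".

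The Statistical analysis section names a single model for outcomes treated as normal: "measures will be analyzed in separate 4 (group: PROfit basic, PROfit plus, PROfit orientation, wait-list control group", crossed with baseline, post-allocation and close-out testing in a repeated-measures ANOVA. If baseline differences are found, "baseline assessment values as well as age and sex discrepancies will be included as covariates in the statistical model". No home, centre or training-group term is named. The fallback Kruskal-Wallis and Friedman tests have none either. The significance level is 0.025.

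The sample size section uses four groups, three measurements, r = 0.60 and f = 0.15, with no ICC or design effect. The Background and Discussion hypothesise that each programme beats the wait-list, that plus beats basic, and that orientation is best.

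**The concern.** The stated analysis does not match the stated randomisation. Plus versus basic and orientation versus plus are comparisons between sets of homes, so their precision depends on how many homes there are and how differently those homes change. The ANOVA judges them against variation between residents, as if each resident had been randomised individually to one of four groups. Pooling the wait-list also sets each programme against controls from all homes, when the design supplies randomised controls in the same homes.

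Training is delivered "in groups of up to 15 participants", a further source of shared change among trained residents.

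At stake is the trial's distinctive claim, the ranking of the three programmes. A significant interaction could arise only because a few homes had a better or worse half-year than others.

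**Working it through.** **The plan's own figure.** For the within-between interaction, λ = f²·N·m/(1 − r). With f = 0.15, m = 3, r = 0.60 and N = 128, λ = 0.0225 × 128 × 3/0.40 = 21.6. On 6 and 248 degrees of freedom at α = 0.05, power is 0.952. Adding 30% gives 128 × 1.3 = 166.4, or 167 per centre, and 3 × 167 = 501. That is within 3% of the stated 513 but not exact. No step contains a term for homes.

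**Inputs taken from the protocol.** 513 residents with 30% dropout leave 513 × 0.7 = 359 completers. Groups of 42–43 per centre (171/4 = 42.75) imply 25% controls. r = 0.60 and the nominal level is 0.025.

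**Inputs assumed, because the protocol does not give them.** 6 to 18 homes, split equally among programmes, and an ICC of change of 0.01 or 0.05. A control share of 50% was also tried. On a scale where residents' variance is 1, an ICC of change of 0.05 is a home-by-time variance of 0.05/0.95 × 0.40 = 0.021 at each occasion.

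**Design effect for a programme-versus-programme contrast.** DE = 1 + (n − 1) × ICC, with n the trained residents per home. With 9 homes, n = 359/9 × 0.75 = 29.9. At ICC 0.05, DE = 1 + 28.9 × 0.05 = 2.45, so 359 completers carry the information of about 359/2.45 = 147. The naive standard error is too small by a factor of √2.45 = 1.57. A test at nominal 2.5% (critical value 2.24) then has a true level of 2 × [1 − Φ(2.24/1.57)], about 15%.

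**Simulation under no effect.** 360 completers, 25% controls, nominal 2.5%, home-by-time variation as above:

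| Homes | 4 × 3 interaction, ICC 0.01 | 4 × 3 interaction, ICC 0.05 | Programme v programme t-test on change, ICC 0.05 |
|---|---|---|---|
| 6 | 8.9% | 43% | 21% |
| 9 | 6.1% | 30% | 16% |
| 12 | 4.2% | 19% | 12% |
| 18 | 3.6% | 13% | 8% |

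With 50% controls, the interaction at ICC 0.05 rejects about 10% (18 homes) to 27% (6 homes) of the time. Repeat runs agree to within two or three percentage points.

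**Where the inflation is small or absent.**
- Home effect constant over time (12 homes): interaction 2.1%.
- Programme versus pooled controls, ICC 0.05, 9 to 18 homes: 6.4% down to 4.4%.
- Programme versus wait-list of the same homes, ICC 0.05: 1.9% to 2.3%.

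**Check of the remedy.** With home-level means of trained residents as the unit, the programme comparison rejects 2.1% to 2.8% over the same range of homes and ICCs. Differencing against same-home controls gives 2.2% to 2.7%.

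**Precision of the two ways to compare programmes.** Take 3 homes per programme, with 90 trained and 30 control residents per programme.
- Direct contrast of trained residents: variance ∝ (2/90)(1 + 29 × ICC).
- Programme × arm contrast: 2 × (1/90 + 1/30)(1 − ICC) = (8/90)(1 − ICC).

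Near ICC 0 the second has √(8/2) = 2 times the standard error of the first. They are equal when 8(1 − ICC) = 2(1 + 29 × ICC), so ICC = 6/66, about 0.09.

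**The case against.** Several stronger readings are tempting, and the protocol does not support them.

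- **Programme comparisons are biased by home.** Homes are randomly assigned to programmes, so the contrasts are unbiased in expectation. The fault is understated variance, which matters most with few homes.
- **P-values are too small whatever the homes are like.** Only home-by-time variation inflates the interaction. The landmark task, which asks "which three landmarks out of a set of ten landmark pictures cannot be found in or around the facility", differs between homes, and so do building layouts. Such differences are mostly stable and cancel in a test of change. The protocol gives no evidence on how differently homes change over time.
- **Every hypothesis is equally affected.** The pooled controls include those from a programme's own homes, so the within-home randomisation is diluted rather than lost. Programme versus pooled control is only mildly inflated.
- **The t-test rates are the plan's error rates.** The planned post-hoc tests are Bonferroni-adjusted, follow only a significant interaction, and read most naturally as pre-post tests within groups. The t-test column illustrates a between-programme comparison and is not a test the protocol clearly specifies.

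It is also fair that the percentages rest on assumed numbers of homes and ICCs, and that a separate analysis plan may exist. That does not answer the core point. The protocol names the model, its factor levels, its covariates and its fallback tests, and that model does not fit the randomisation it describes.

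**Conclusion.** The point stands in conditional form. The structural mismatch is certain from the text. Whether it inflates type I error, and by how much, depends on home-by-time variation and the number of homes, neither of which the protocol states. Under the assumptions above, the omnibus interaction rejects a true null about 4% to 9% of the time at an ICC of change of 0.01, and about 13% to 43% at 0.05, against a nominal 2.5%. Since the post-hoc tests appear to be within-group, this omnibus test is the main planned evidence on differences between programmes.

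The harm is mainly to type I error. At the effective sample sizes for 9 to 18 homes and ICCs up to 0.10, power for f = 0.15 at α = 0.05 stays at about 0.84 or more, before the loss of degrees of freedom. The analysis should be changed before the data are analysed.

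**What to change.** Replace the 4 × 3 ANOVA by a linear mixed model with home and home-by-time effects, adding a training-group effect in trained residents if it can be estimated. Then:

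1. Estimate each programme against the wait-list of the same homes.
2. Test plus versus basic and orientation versus plus as between-home comparisons, with small-sample degrees of freedom based on the number of homes. Either the mixed model or home-level means will do.
3. If wanted, add programme × arm contrasts against same-home controls as a supporting analysis. Note that they are less precise than the direct contrast unless the ICC of change exceeds about 0.09 (3 homes per programme, 3:1 allocation).
4. State that conclusions on programme ranking rest on the number of homes.

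The cost is wider intervals for the programme-versus-programme comparisons and slightly more modelling. In the direct contrast the extra width reflects variation between homes. In the programme × arm contrast much of it comes from the choice of estimator. No new data are needed.

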#### Assignment of interventions

To avoid selection bias, stratified randomization will be conducted to divide participants into an intervention group and a wait-list control group. The random allocation will be stratified according to sex, age, and cognitive performance to avoid differences in the baseline conditions between the groups. Data collection will be done by blinded assessors; data will be stored securely and in pseudonymized form using a coded ID number to maintain participants’ confidentiality. To avoid performance bias, the measurements and the interventions follow a standardized protocol.

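### The group × test ANOVA has no home term, although residents are randomised within homes, so the standard error for each programme versus wait-list is too small

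*Protocol article*

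**What the plan says.** Allocation has two levels. Under Trial design, "The type of intervention program will be randomly assigned to the participating nursing homes"; residents' "allocation to the intervention or wait-list control group will be randomized after baseline assessment in each nursing home". The abstract confirms one programme per home. The Interventions section says that wait-list residents keep to their usual activities for twelve weeks "until they receive the intervention type which was randomly assigned to the nursing home". Each programme therefore has its own wait-list residents in its own homes. Assignment of interventions stratifies the resident-level allocation by sex, age and cognitive performance "to avoid differences in the baseline conditions between the groups".

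The Statistical analysis section uses one group factor with a single wait-list level: "4 (group: PROfit basic, PROfit plus, PROfit orientation, wait-list control group) × 3" (tests). It names no home, centre or programme-of-home term. Covariates enter only if baseline differences are detected, in which case "baseline assessment values as well as age and sex discrepancies will be included as covariates in the statistical model". The Kruskal-Wallis and Friedman fallback has no home term either.

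**The concern.** The trial's first hypothesis is that each programme does better than wait-list. The design protects that comparison well, because trained and wait-list residents share a home and anything that moves the whole home over twelve weeks affects both. The planned model does not use this. A programme's trained residents, all from that programme's homes, are set against wait-list residents from every home. A home-wide change then reaches all of the trained group but only part of the control group, and the ANOVA has nowhere to put it except the residual. Its tests treat residents as independent, so p-values come out too small and confidence intervals too narrow. Because the article states this model in full and sizes the trial for it, it is a choice already made and not a detail left to a later plan.

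**Working it through.** **Inputs from the protocol.** 513 participants in three centres, four groups, 42–43 per group per centre (Sample size estimate); significance level 0.025 (Statistical analysis). The group size reproduces: 513/12 = 42.75 per group per centre, or about 128 per group. The total of 513 does not follow from the stated power inputs, which give 127 before dropout (128 with equal groups) and 128/0.7 = 183 after it. That is a separate matter; only the group sizes are used here.

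**Inputs assumed.** The number of homes and the share ρ of the variance of change that lies between homes are not given. All four groups appear in each of three centres and each home runs one programme, so each centre needs at least three homes, nine in all. I take 9 and 18 homes (J = 3 and 6 per programme) and ρ = 0.02, 0.05 and 0.10, with total variance of change set to 1.

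**Step 1: where the controls live.** With an even spread, 128/3 ≈ 43 wait-list residents come from a given programme's homes and about 86 (two thirds) from other homes. Without an even spread, at most one programme can supply more than half of the pooled controls.

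**Step 2: home variance in the contrast.** In (programme mean − pooled wait-list mean), each of the programme's J homes has weight 1/J − 1/(3J) = 2/(3J), and each of the other 2J homes has weight −1/(3J). The multiplier of the home variance is

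J·(2/(3J))² + 2J·(1/(3J))² = 2/(3J).

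For trained minus wait-list within the same homes it is 0.

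**Step 3: true against stated standard error.** Stated SE = √(2/128) = 0.125. True SE = √[(1−ρ)·2/128 + ρ·2/(3J)]. Actual error rate = 2·[1 − Φ(2.241 / ratio)], where ratio is true SE over stated SE.

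| Homes | ρ | True SE | Ratio | Error rate at nominal 0.025 |
|---|---|---|---|---|
| 9 | 0.02 | 0.141 | 1.12 | 0.046 |
| 9 | 0.05 | 0.161 | 1.29 | 0.082 |
| 9 | 0.10 | 0.190 | 1.52 | 0.141 |
| 18 | 0.02 | 0.132 | 1.06 | 0.034 |
| 18 | 0.05 | 0.143 | 1.14 | 0.050 |
| 18 | 0.10 | 0.159 | 1.27 | 0.077 |

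A separate simulation at nominal 0.05 shows the same pattern. With 4 homes per programme the pooled contrast rejects in 10.4% of null trials at ρ = 0.05 and 15.4% at ρ = 0.10. The within-home contrast stays between 4.4% and 5.5% in every setting tried.

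**Step 4: what each model costs.** Generalised least squares, 9 homes, 43 trained and 14 wait-list residents per home, SE of one programme against wait-list:

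| ρ | Four-level group + random home | Four-level group + fixed home | Programme (3) × arm (2) + random home |
|---|---|---|---|
| 0 | 0.125 | 0.178 | 0.178 |
| 0.02 | 0.137 | 0.176 | 0.176 |
| 0.05 | 0.146 | 0.173 | 0.173 |
| 0.10 | 0.151 | 0.169 | 0.169 |

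Against 0.125, the random-home model costs a factor of 1.10, 1.17 and 1.21 at ρ = 0.02, 0.05 and 0.10. At each of these values its SE is also below the true SE of the planned contrast in step 3.

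**The case against.** The strongest reply is that a single wait-list level is sound. Until T2 all wait-list residents get the same thing, so one control mean is a fair model. That stands. The pooling is not the fault; the missing home term is. With fixed home-by-test terms added to the same four-level factor, each programme's coefficient becomes its own-home trained-minus-wait-list difference.

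A reader might infer that the pooled comparison is biased or confounded. If one programme's homes would change by D more than the others whatever they were given, the contrast is off by D − D/3 = 2D/3. But programmes are randomised to homes, so D averages zero over that randomisation. It is chance imbalance that the standard error should carry and does not.

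A reader might also point to buildings, facility-specific landmark tests and life-space zones. Features that shift a home's level equally at every visit drop out of the group × test interaction, so only differences in change count. The protocol does not document how large those are. It also places all four groups in every centre, which balances region.

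Lastly, the contrast in step 3 is not a test that the protocol names. It plans the omnibus interaction, then baseline-to-post tests within groups. That is correct, but the omnibus is affected too: simulated on T1–T2 change with 9 homes and ρ = 0.02, it rejects in about 12% of null trials at nominal 0.025. Part of that comes from programme-versus-programme differences, which are between homes by design and which no re-pairing of controls can repair.

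**Conclusion.** The point holds as a fault of variance. The planned model ignores the home, although the home is the unit to which programmes are randomised and the block within which residents are randomised. For a programme against the pooled wait-list, the real error rate at nominal 0.025 is about 5%, 8% and 14% with 9 homes, and 3%, 5% and 8% with 18, at home shares of 0.02, 0.05 and 0.10. With many homes and a small share the effect is minor; with the fewest homes that the group sizes imply, it is not. The figures rest on the assumed number of homes and home share, an even spread of wait-list residents over programmes, and about 128 residents per group before dropout. The documents do not support a claim of bias, nor a need to abandon the four-level factor for the comparison at T2.

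**What to change.** Keep the four-level group factor and add a random home-by-test effect. Include sex, age and cognitive performance as prespecified covariates, since they are the stratification factors, instead of letting covariates depend on a baseline test. State that each programme versus wait-list is estimated at T2 from this model. The restriction to T2 matters because wait-list residents afterwards receive their own home's programme, so the single wait-list level no longer describes one condition at T3. Report the fixed-home version as a sensitivity analysis; it rests only on the within-home randomisation. The random effect also gives programme-versus-programme comparisons an honest standard error. The rank-test fallback has the same gap and needs a form that accounts for home.

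No data collection changes, provided home is recorded. The cost is slightly more analysis work and wider, honest standard errors: with 9 homes and four equal groups, about 1.10 to 1.21 times the stated one for the random-home model at shares of 0.02 to 0.10. The fixed-home sensitivity analysis costs up to √2 = 1.41 times if homes do not differ at all. Recoding to programme of the home by arm is unnecessary and does not help: even with a random home effect its SE at share 0 is 0.178 against 0.125, because other programmes' controls then add nothing.
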